### Potential risks and hazards to participants and how these are being minimised

Acupuncture and Alexander Technique lessons are relatively safe interventions. However we will involve all practitioners in an induction event prior to their providing sessions for participants within the trial. We will document the procedures designed to minimise the key risks and will induct practitioners into the trial documentation. For acupuncture, the current evidence is that the modality is very safe when practised by competent practitioners. Expected adverse events that have been associated with acupuncture include nausea, fainting, dizziness, sweating, vomiting, bruising, numbness and bleeding at the site of needling, stiffness, headache or migraine, sleeplessness, aggravation of existing symptoms, drowsiness or tiredness after treatment (which might be a concern if participants are driving home), diarrhoea, and emotional reactions, such as anxiety and panic [22,23]. Likewise, for Alexander Technique lessons, the risks are very low as the manual aspects of the lessons involve guidance, not manipulation as generally understood, and are very gentle. Possible adverse events associated with Alexander Technique lessons include transient dizziness during a lesson, tiredness usually beginning 1 to 2 hours or more after a lesson, and muscle aches (similar to those post-exercise). For the population as a whole, expected hospital admissions might occur due to musculoskeletal injuries, cardiovascular disorders, gastrointestinal disorders, respiratory disorders, cancer-related care, exacerbation of existing medical conditions and elective surgery. We will use the standard operating procedures of the York Trials Unit for monitoring and reporting adverse events. Reporting on serious and non-serious adverse events will involve participants, practitioners and GPs.

### Inclusion/exclusion criteria

We will be recruiting typical patients who have consulted their GP for chronic neck pain and are being managed in primary care. Patients will be identified via GP databases, identifying potential participants from relevant READ codes, as adapted from our pilot study [6]. We will also identify some patients through advertisements placed in GP practices. Eligible patients will be aged 18 years and older. They will have had neck pain for at least 3 months, which fits with current thinking on what constitutes ‘chronic’ neck pain, [1] such that outcome data at this time point will be consistent with that in systematic reviews [24,25]. Given that patients are likely to have disability as well as pain, we will have a 28% minimum cut-off score on the Northwick Park Questionnaire (NPQ), based on the cut-off at 10 points (out of 36), the same as we used in our physiotherapy trial [26]. We will exclude patients with: serious underlying pathology; prior cervical spine surgery; history of psychosis; rheumatoid arthritis ankylosing spondylitis; osteoporosis; haemophilia; cancer; HIV or hepatitis; alcohol or drug dependency currently or in the last 12 months; actively pursuing compensation or with pending litigation; currently receiving acupuncture for neck pain; or having attended one-to-one Alexander Technique lessons in the last 24 months. We will exclude patients at baseline if they are pregnant, not because of risks associated with the interventions, but because of potential loss to follow-up. Participants who become pregnant after entry in to the trial will remain in the trial and continue to attend the intervention. We will exclude patients who have participated in a clinical trial in the previous year if there is potential confounding, or if the burden for the patient appears to be too great. Reasons for exclusions will be documented and reported.

People who are unable to speak or who find it difficult to communicate in English will be excluded from the study. A reasonable level of understanding of English is essential to engage in the sessions with an English-speaking practitioner, to sufficiently understand the practitioners who takes her/his case history, and to understand explanations of the acupuncture treatment or Alexander Technique lessons. No funds have been provided within the research grant to pay for the translation of materials into other languages or to cover costs associated with the use of interpreters, nor does the research team have established access to such services. Therefore while the translation of trial materials into other languages, or the use of interpreters, might enable a small number of patients who do not understand or speak English to take part in the study, in all likelihood this would be neither financially feasible nor practical.

### Proposed duration of treatment/intervention period

The trial is designed to be a pragmatic one, whereby practitioners will be encouraged to provide care in a way that, as close as possible, reflects their normal practice. We provided guidance for both the Alexander teachers and the acupuncturists on the number of sessions available within the trial, and the flexibility in delivering these sessions in terms of frequency. Alexander teachers and acupuncturists will be able to discharge participants who they believe will receive no further short or long-term benefit of continuing. However we gave no guidance on a minimum number of sessions prior to discharge.

The proposed trial will provide participants allocated to the offer of acupuncture a course of up to twelve 50-minute sessions, usually weekly initially and fortnightly towards the end of the series. We expect the acupuncture to be delivered within a five-month period.

Participants allocated to the offer of Alexander Technique lessons will attend up to twenty 30-minute lessons. Generally, lessons will be weekly, with the option of being twice weekly initially and fortnightly towards the end of the series. We expect the lessons to be completed within five months.

### Proposed frequency and duration of follow-up

Questionnaire-based data will be collected at baseline, and then at 3, 6 and 12 months post-randomisation. For the first six months we will also collect a single fortnightly pain score by text message (SMS), then monthly until 12 months, so that we can plot the trajectory of any change over this period.

### Primary outcome measures

The primary outcome measured at baseline, 3, 6 and 12 months will be the Northwick Park Neck Pain Questionnaire [27], with the primary endpoint at 12 months. We used this outcome measure in both our physiotherapy for neck pain trial [24] and our acupuncture for neck pain pilot [6]. A secondary time point will be at 6 months, and an area-under-curve analysis will include 3, 6 and 12 month time-points.

### Secondary outcome measures

Secondary outcome measures will be the Short Form (SF) -12v2 [28] for quality of life [28], and EQ-5D [29] as health utility measure, both completed at baseline, 6 and 12 months. A measure of present pain intensity will be collected fortnightly by text message for the first six months of the trial, and monthly thereafter until the 12 months’ endpoint. Participants who consent to respond with text messages will receive £5 as an up-front payment to cover costs. Adverse event data and beneficial effects which may be related to the intervention will be collected at 3, 6 and 12 months. Additionally, throughout the trial we will collect data on all adverse events using the Standard Operating Procedures of the York Trials Unit.

### Treatment/intervention effect modifiers

A treatment/intervention effect modifier is a variable that provides an interaction, such that the effect of X on Y depends on the level of this additional variable. No causal sequence is implied by an interaction. For example, an intervention may be successful for males but not for females. This is called an interaction effect. To explore potential treatment/intervention effect modifiers, we will collect data at baseline on the participants’ age, gender, education and employment, income band, and ethnicity as well as preferences, expectations and beliefs about the interventions. We will also collect preference data at final follow-up to examine if these change post-intervention.

### Treatment/intervention effect mediators

A treatment/intervention effect mediator involves a variable that implies a causal sequence, intervention → mediator → outcome. We will add self-report measures that are designed to quantitatively explore mediators that might contribute to longer term change. At baseline, 6 and 12 months we will collect data on the following potential mediator variables:

1) self-efficacy, using the five-question pain management sub-scale of the Chronic Pain Self-Efficacy Scale [30], modified to be consistent with subsequent changes to the original scale by replacing the 0 to 10 scale with 0 to 8 and replacing ‘certain’ with ‘confident’ [31,32]. At 6 and 12 months we will add the question, ‘Can you use/apply things you have learned from the intervention/care in everyday life situations to reduce pain?’, a question modified from one used to assess self-management in a previous neck pain trial [33]. Consistent with data collected in previous research into unanticipated benefits of complementary therapies for back pain[34], we will also add at 6 and 12 months the questions, ‘What effect, if any, has the treatment/care you have received for your neck pain had on you in the last 6 months? For example this might include your thoughts, feelings, reactions or activities’ and ‘Have you changed anything you do in the last 6 months as a result of the treatment/care you have received?’

2) stress management, using the four-question Perceived Stress Scale (PSS) [35,36] because psychosocial stressors are linked to musculoskeletal problems [37], and in particular mental stress increases the risk of having neck pain [38]. Related to this we will measure ‘flow’, using the two-question General Flow Index [39], as flow is considered a mechanism in traditional Chinese medicine for reducing stress-related conditions [40] and teachers report that flow is facilitated by lessons in the Alexander Technique.

3) incorporation of practitioner advice about self-care and/or life-style. We build on evidence on the role of self-care advice associated with acupuncture treatment [7] and Alexander lessons by asking, ‘During the treatment/care you received in the last 6 to 12 months, did you learn to improve the way you live and care for yourself?’, and ‘If you answered yes, what were the changes that you were advised or taught how to make?’(open question), and ‘To what extent are you able to put into practice the advice or teaching you received?’(scale 0 to 100), and ‘To what extent are the changes you have been making helpful to you?’(scale 0 to 100).

### Cost effectiveness

The economic evaluation will be undertaken primarily using an NHS perspective, as recommended by the National Institute for Health and Care Excellence (NICE) [41], and secondarily using a societal perspective. In all three arms we will collect data on health service resource use, including hospital and GP visits and medication at baseline, 6 and 12 months. We will use a resource-use questionnaire tailored to include services typically used by this population. We will seek the consent of participants to access their medical records and if needed check with individuals’ GPs with regard to consultations and interventions. Quantities of services used will be multiplied by national unit cost estimates to estimate cost profiles for patients in the trial. We will also collect data on private health care used (including acupuncture, Alexander Technique lessons and other private care), as well as productivity related costs, such as days off work due to neck pain. The cost of productivity changes will be presented separately in accordance with NICE guidelines.

The base case evaluation will combine intervention-related costs and wider NHS costs with changes in QALYs, derived from EQ-5D, to perform a cost-utility analysis in the format recommended by NICE. We will estimate incremental cost-effectiveness at 12 months by calculating the cost and QALY differences in the active intervention arms over and above the control. Cost and outcome data will be bootstrapped to adjust for skewness in the trial data. Data generated from the bootstrapping will be used to generate cost-effectiveness acceptability curves to demonstrate uncertainty around the cost-effectiveness ratio, based on different monetary values being attached to QALYs. In addition, as utility measures can be relatively insensitive to smaller changes in health status [42], we will use the NPQ as a secondary outcome measure.

Exploratory analyses drawing on patient preferences will be conducted to observe whether cost-effectiveness differs by the preference participants expressed for the interventions prior to randomisation.

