### The principal research questions to be addressed

Our principal research question asks: What is the clinical and economic impact when comparing acupuncture treatment plus usual care to usual care alone, and Alexander Technique lessons plus usual care to usual care alone in patients with chronic neck pain who are recruited from primary care? We will also compare acupuncture to Alexander Technique lessons to estimate possible clinical differences. We will determine whether putative benefits are clinically worthwhile. We will compare the cost-effectiveness of the alternative strategies, and if these interventions are at an additional cost to usual care, then we will ascertain whether they are worth paying for in terms of cost per Quality Adjusted Life Year (QALY) gained, in the context of the National Institute for Health and Care Excellence (NICE) threshold, which ranges from £20,000 to £30,000 [5]. We will also assess the acceptability and safety profile of acupuncture and Alexander Technique lessons for this patient group. In this study, we have used our pilot trial on acupuncture for chronic neck pain (ISRCTN06223266) [6] to inform the design of the full-scale trial.

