## Methods/Design

### Details of the trial

The study is a three-arm pragmatic randomised, controlled trial to evaluate the effectiveness, cost effectiveness, safety and acceptability of acupuncture and Alexander Technique lessons for patients with chronic neck pain. The three arms are: acupuncture plus usual care, Alexander Technique lessons plus usual care, and usual care alone. Participants will be recruited from primary care and randomised to one of the three arms after we have obtained their informed consent to participate in the trial and their completed baseline questionnaire and after they have been screened for eligibility.

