### Proposed sample size and a description of the power calculations

We will recruit 500 participants in total to the trial. Our sample size calculations were performed for a simple comparison of two groups. From our pilot, the standard deviation of the primary endpoint, the Northwick Park Questionnaire (NPQ), was 16%, and the correlation between baseline and 3-month NPQ was 0.69 [6]. A clinically meaningful difference on the NPQ is 5 percentage points [43], a 0.31 effect size. With 90% power and alpha = 5% we would require 113 participants per arm after adjusting for baseline. We are aiming for a loss to follow-up of 20% but in our estimate of sample size we are conservative, allowing for 30% loss to follow-up. Randomising into three equally sized groups, our required total sample size will be 500.

For our primary comparison, we will estimate the difference in mean score from the NPQ at 12 months between the acupuncture and control groups and between the Alexander Technique lessons and control groups, after adjustment for baseline pain score using analysis of covariance. Each of our two active interventions tested against control can be interpreted quite independently of the other. This does not constitute a problem of multiple testing, as there might be if we had two different kinds of acupuncture. If we find acupuncture to be significantly better than the control, then we would conclude that it worked. But this test would tell us nothing about Alexander Technique lessons versus control. Therefore when testing two independent hypotheses, we do not need to use multiple comparison procedures. We will, as a secondary analysis, estimate the clinical difference between acupuncture and Alexander Technique lessons.

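### The economic method gives each active arm's cost-effectiveness against usual care only, so it does not deliver the stated further aim of comparing the alternative strategies with one another

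*Protocol article*

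**What the plan says.** The trial compares three options: "The three arms are: acupuncture plus usual care, Alexander Technique lessons plus usual care, and usual care alone". There is no combined arm.

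The section on the principal research questions sets the main clinical and economic question as two contrasts, "comparing acupuncture treatment plus usual care to usual care alone, and Alexander Technique lessons plus usual care to usual care alone". It then adds a head-to-head comparison with a clinical purpose: "We will also compare acupuncture to Alexander Technique lessons to estimate possible clinical differences". The next economic aim is broader: "We will compare the cost-effectiveness of the alternative strategies". Value for money is to be judged against the NICE threshold, "which ranges from £20,000 to £30,000" per QALY.

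The Cost effectiveness section gives one calculation of incremental cost-effectiveness, at 12 months: "calculating the cost and QALY differences in the active intervention arms over and above the control". It calls for a cost-utility analysis in NICE's format, with bootstrapped costs and outcomes. Acceptability curves are to show the uncertainty around the cost-effectiveness ratio.

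The sample size section again limits the head-to-head comparison to clinical outcome: "We will, as a secondary analysis, estimate the clinical difference between acupuncture and Alexander Technique lessons".

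**The concern.** With three options for the same patients, two ratios against a common control do not show which option is the best value. The ratio for the costlier and more effective active arm credits it with health gains that the cheaper active arm may already deliver. What bears on a choice between the two is the extra cost per extra QALY of the costlier arm over the cheaper one, and the method as stated does not produce that.

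The stakes are practical. The article says that the results should inform policy makers, providers and commissioners, and its design section makes worthwhile cost-effectiveness one of four minimum requirements for a positive pragmatic trial. If both active arms pass against usual care, a commissioner deciding which to fund would have no planned estimate of the difference in value between them, and no measure of its uncertainty.

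**Working it through.** **The plan's own figures.** The article reports no cost, QALY or cost-effectiveness figure, so there is nothing to reproduce on this point. The only numerical input it supplies is the threshold of £20,000 to £30,000 per QALY. All costs and QALY gains below are assumptions, and the labels A (cheaper) and B (costlier) could fall on either active arm.

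**Formulas.**
- Ratio against usual care = ΔC / ΔQ, where ΔC and ΔQ are the arm's mean cost and QALY differences from usual care.
- Ratio of B against A = (ΔC_B − ΔC_A) / (ΔQ_B − ΔQ_A).
- Net benefit at value λ per QALY = λ × ΔQ − ΔC.

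**Illustration 1.** A: +£450, +0.030 QALY. B: +£700, +0.036 QALY.
- A against usual care: 450 / 0.030 = £15,000.
- B against usual care: 700 / 0.036 = £19,444.
- B against A: (700 − 450) / (0.036 − 0.030) = 250 / 0.006 = £41,667.
- Net benefit at £20,000: A 600 − 450 = £150; B 720 − 700 = £20.
- Net benefit at £30,000: A 900 − 450 = £450; B 1,080 − 700 = £380.

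Both arms pass at £20,000 against usual care, yet B fails against A even at £30,000.

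**How wide is the region of reversal?** Hold A and B's cost as above and vary B's QALY gain.
- At £20,000, B passes against usual care from 700 / 20,000 = 0.035. It fails against A below 0.030 + 250 / 20,000 = 0.0425.
- At £30,000, the limits are 700 / 30,000 = 0.0233 and 0.030 + 250 / 30,000 = 0.0383. At or below 0.030, B is dominated.
- Above the upper limits there is no reversal.

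**Illustration 2, with different inputs.** A: +£300, +0.030 QALY (£10,000 per QALY). B: +£600, with its QALY gain varied.

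| B's QALY gain | B against usual care | B against A |
|---|---|---|
| 0.030 | £20,000 | dominated |
| 0.035 | £17,143 | £60,000 |
| 0.040 | £15,000 | £30,000 |
| 0.045 | £13,333 | £20,000 |
| 0.050 | £12,000 | £15,000 |

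B is at or below £20,000 against usual care in every row. Against A it runs from dominated to clearly acceptable.

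**Uncertainty.** A simulation took the 0.035 row with 117 patients per arm (500 × 0.7 / 3), an assumed QALY SD of 0.2 and an assumed cost SD of £800, treated as independent and normal.

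| Value per QALY | A beats usual care | B beats usual care | Best of three: usual care / A / B |
|---|---|---|---|
| £20,000 | 0.71 | 0.57 | 0.19 / 0.53 / 0.28 |
| £30,000 | 0.78 | 0.72 | 0.12 / 0.51 / 0.37 |

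The two pairwise probabilities add to more than 1 and do not give the chance that an arm is the best of the three. That needs the three arms evaluated together.

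**The case against.** The case on the other side is substantial, and much of it stands.

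- **The stated ratios answer the principal question.** That question is each active arm against usual care. A reader might infer that ratios against control are the wrong analysis and should be demoted. The article does not support that: they are valid for the question it puts first.
- **The threshold is tied to usual care.** The sentence that promises to compare the strategies goes on to ask whether any additional cost over usual care is worth paying. That weakens a reading of the threshold as a test between the active arms. It does not remove the opening clause, which promises a comparison of the strategies.
- **The point estimate is recoverable.** With a common control, the cost and QALY differences between the active arms follow by subtraction, as in the working above. The probability that each arm is the best of the three does not follow in that way.
- **A condensed article may leave this to a fuller plan.** A health economics plan may well contain the three-way analysis, and the article does not rule it out. But this is more than silence: the article names control as the comparator and twice describes the head-to-head comparison as clinical. The reference to NICE's format does not itself state a three-way analysis.
- **The options need not exclude one another.** A reader might infer that only one intervention could be adopted. The article never says so. Both are add-ons to usual care, and a commissioner might offer both as referral options, in which case each ratio against usual care is also decision-relevant.

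**Conclusion.** The point holds in a limited form. The method in the Cost effectiveness section serves the principal economic question but falls short of the article's further aim of comparing the alternative strategies. It yields no planned head-to-head economic result and no joint statement of uncertainty.

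Its size cannot be fixed from the article. Under the assumed figures, an arm at £17,143 to £19,444 per QALY against usual care can cost £41,667 to £60,000 against the other active arm. Under other plausible-looking figures, the same arm remains good value on both comparisons. Reversal occurs when the costlier arm's extra QALY gain over the cheaper one is small relative to its extra cost.

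A reader might go further and infer that the trial will reach a wrong adoption conclusion. The article does not support that: no cost or QALY data are given, and it sets no rule for choosing between the active arms.

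**What to change.** Keep the two ratios against usual care as the answer to the principal question. Add to the Cost effectiveness section, for the aim of comparing strategies, one of two equivalent approaches:

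- a fully incremental analysis: rank the three arms by mean cost, remove dominated and extendedly dominated options, and compute each ratio against the next remaining option; or
- net benefit for all three arms across the threshold range.

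In either case, bootstrap the three arms together and draw one acceptability curve per arm, with the three probabilities summing to 1 at each value of a QALY.

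The cost is a short change of wording and a little extra analysis and reporting. Resource use and EQ-5D are already to be collected in all three arms, so no new data, patients or follow-up are needed. If a separate health economics plan already contains this analysis, one sentence in the protocol saying so would be enough.
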